### Data monitoring

Adverse events include fainting, bent needles, and subcutaneous hematomas during ocular acupuncture, tinnitus, chest tightness, palpitation induced by fMRI scanning noise, and muscle pain and weariness caused by excessive exercise training.

An independent data monitoring committee (DMC) comprised of a study statistician, external stroke researcher, and external rehabilitation therapist will oversee the study and review adverse events. The DMC will constantly monitor the entire study procedure and make suggestions for quality assurance, as well as consider and recommend either stopping or continuing the study if adverse events occur. Once the study or data analysis is finished, the study team will be unblinded.

### Auditing

Once a year, independent staff from the Chengdu University of Traditional Chinese Medicine will monitor and audit the prudent use of project money.

## Discussion

A major side effect of the cerebrovascular accident is PSD, which impairs motor function and places a heavy financial, psychological, and physical burden on patients, families, and society. Rehabilitation after a stroke is crucial to maintaining overall health. Sun (49) verified the superior effects of acupuncture combined with exercise training on neurological function and movement problems in patients with cerebral infarction compared to exercise training alone by measuring Fugl-Meyer score, BI score, Berg score, and NISS score changes (*P* < 0.05). The combination therapy can play a better role in terms of effectiveness and symptom function improvement, with fewer adverse events and good safety, compared to acupuncture or Bobath therapy alone, according to Liu's systematic review of spastic paralysis after stroke (50). The greatest improvement in motor function can be achieved when acupuncture is used in conjunction with exercise training. However, this approach necessitates acupuncture manipulation first, followed by training, which hinders patient long-term perseverance and has an impact on follow-up rehabilitation due to the lengthy treatment time, numerous manipulated meridians and acupoints, obvious pain sensations, and complex steps. By combining ocular acupuncture and exercise training simultaneously, OAKT can ease limb spasms, decrease muscle tension, alleviate motor dysfunction, etc. in PSD patients with improved outcomes. It can minimize the treatment duration and rehabilitation course, and improve short- and long-term efficacy by making use of the advantages of fewer stimulation acupoints, low pain feelings, simple manipulation steps, rapid onset, and high patient tolerance. Unfortunately, due to the short application period, it is yet unclear how OAKT promotes PSD recovery, necessitating urgent research in this area. Therefore, the first scientific challenge of this work is how to appropriately conduct the OAKT mechanism research on PSD.

Through the exchange and fusion of matter, energy, and information, the brain, the higher neurological center, can regulate various functional activities of peripheral organs. The M1-THA-SPC, a crucial input-output pathway of motor neuron signal transmission, can assist in limb goal-oriented motor control, achieving motor proficiency, coordinating movement, and motor learning through the mapping of neurons. Muscle serves as both the peripheral target organ and the primary executive body of the movement in this signaling pathway, the function cannot be carried out without the command and regulation of the higher and secondary centers (brain and spinal cord) (SPC). As a result, we intend to conduct a central-peripheral linkage control study in conjunction with brain-spinal cord regulation and muscular response to understand the mechanism of OAKT on PSD.

fMRI, a non-invasive neuroimaging technique for studying cerebral function, can quantitatively detect the functional activity of brain neurons to reflect the functional state of the brain objectively. Previous fMRI studies have shown that the function of motor-related brain areas, particularly the primary motor cortex, as well as the degree of linkage between the thalamus and other cortical motor networks, is aberrant in stroke patients, and changed dramatically after acupuncture intervention. TMS-MEP is a type of neurotic electrophysiological detection method for recording compound action potentials on the appropriate muscles by transcranial magnetic stimulation of cortical motor cells, spinal nerve roots, and peripheral nerves. It can objectively reflect the current state of cerebral cortex function and is useful in assessing subjects' motor neural function and prognosis. For these reasons, this study will combine fMRI scanning with TMS-MEP detection to realize brain-spinal cord regulation and muscle response linkage control mechanism research, as well as completely investigate the central-peripheral coupling effect of OAKT on PSD.

Two advances in this study are the idea and the methodology. For the idea, we propose to conduct a prospective functional neuroimaging and neurotic electrophysiological study based on a case-control study in the PSD and HC groups as well as a self-control study in the PSD group. The primary motor cortex (higher center), the thalamus (higher center), the spinal cord (secondary center), and the muscle (peripheral) motor neural signal transmission channel are the targets of our assessment of PSD's abnormal central-peripheral neural function and the coupling effects of OAKT on PSD. For the technique, we propose doing a curative effect evaluation and mechanism investigation based on fMRI scanning, TMS-MEP examination, and the MMT and Fugl-Mayer scale assessment to examine the effects of OAKT on brain function, motor nerve function, and degree of motor dysfunction in PSD. Pearson analysis will also be performed between the MMT score, Fugl-Meyer score, and ReHo values of PSD to investigate the association of imaging, neurotic electrophysiological, and clinical outcomes, and to finally exploit the central-peripheral linkage control mechanism and coupling effect of OAKT on PSD from functional imaging and neurotic electrophysiology perspectives.

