## Methods

### Study setting

This is a prospective functional neuroimaging and neurotic electrophysiological study with a case-control design between the PSD with the HC groups and a randomized controlled design within the 3 PSD groups (OAKT group, ocular acupuncture group, and kinesitherapy group). Using fMRI scanning and the TMS-MEP technique, we will assess the central-peripheral neuronal function changes of PSD as well as the coupling effects of OAKT on them. This trial was authorized by the Institutional Review Board of Chengdu University of Traditional Chinese Medicine in April 2022 (reference number: 2022KL-027) and registered (ChiCTR2200060483) at the Chinese Clinical Trial Registry in June 2022. We plan to enroll 90 participants at the Hospital of Chengdu University of Traditional Chinese Medicine from Aug 31, 2022, to Dec 31, 2023. All eligible subjects will be evaluated by fMRI scanning, TMS-MEP examination, and the MMT and Fugl-Mayer assessment following enrollment and on the last day after 4-weeks of waiting (for HC subjects) or intervention (ocular acupuncture, kinesitherapy, or OAKT for PSD subjects, respectively). MMT and Fugl-Meyer score, ReHo value, cluster size, active or positive brain regions and their MNI coordinates, amplitude (AMP), potential latency (PL), and central motor conduction time (CMCT) in the cortical region will be measured, and Pearson correlation analysis will be performed to assess the relationship between clinical and imaging outcomes. This trial will be conducted in accordance with the Standard Protocol Items: Recommendations for Interventional Trials (SPIRIT) (43). Figure 1 displays a flow diagram.

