### PSD participants

This study will exclude dyskinesia brought on by progressive supranuclear palsy, hepatolenticular degeneration, essential tremor, multiple system atrophy, chorea, tossing syndrome, myoclonus, dystonia, Tourette syndrome, and other conditions.

PSD participants that meet the following criteria: (1) have unilateral dyskinesia and a fresh stroke diagnosis; (2) are right-handed and aged 30–80; (3) have no fMRI or TMS contraindications, and no metallic objects inside the body; (4) haven't undergone acupuncture or exercise therapy for a disease-related condition in the previous month; (5) comprehend and agree with the relevant research content and volunteer to sign the informed consent form can be included in this study. While those who (1) have serious illnesses like uncontrollable hypertension, arrhythmia, serious coronary heart disease, uncontrolled diabetes complications, epilepsy, serious organ failure, and a second stroke, etc.; (2) have unstable vital signs; (3) are vulnerable to co-infection, bleeding, tumor, pregnant women, and postoperative dysfunction; (4) receive other Traditional Chinese Medicine rehabilitation interventions besides acupuncture during treatment; (5) with linguistic or cognitive impairment; (6) with a history of mental illness or long-term sedative use; (7) with conditions that prevent exercise will be excluded.

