### Interventions

PSD participants will be randomized to the ocular acupuncture (OA) group, the kinesitherapy (KT) group, or the OAKT group after enrollment.

Subjects in the OAKT group will undergo kinesitherapy after receiving ocular acupuncture stimulation at the “Upper-Jiao Area” (ACU 1), “Lower-Jiao Area” (ACU 2), “Liver Area” (ACU 3), and “Kidney Area” (ACU 4) (16) (Figure 2). This involves a series of advised exercise training consisting of warm-up exercises (low levels of aerobic exercise), exercise training (including aerobic training, walking training, treadmill training, resistance training, upper limb flexion adduction-abduction exercise, lower extremity knee flexion-extension exercise, flexibility training), and relaxation training (stretching exercise) (46). Needles for ocular acupuncture will remain embedded until the day's exercise training is finished. OAKT will be manipulated once a day, 5 days a week, for 4 weeks, with 2 days off between courses. Sweating, breathing, pulse, and blood pressure measures will be used to adjust the exercise prescription.

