**Figure 2 F2:**
[figure not shown]
Location of ocular acupoints.

Subjects in the OA group will receive ocular acupuncture stimulation at the same acupoints of that in the OAKT group, without any exercise training of any kind.

Subjects in the KT group will undertake the same kinesitherapy as well as that in the OAKT group, without ocular acupuncture stimulation.

Healthy subjects will only get clinical, functional imaging, and electrophysiological evaluation without any therapy after enrollment and on the last day of the fourth week.

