#### Correlation analysis between clinical and imaging data

The MATLAB software will be used to conduct the correlation analysis between ReHo values and clinical indexes of PSD. Gender, age, and course will be included as covariates in a Pearson correlation study between the MMT score, Fugl-Meyer score, and ReHo values of PSD. The statistical threshold of *P* < 0.05 will be considered statistically significant.

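### The Discussion calls the patient part a self-control study and ReHo has only a paired test, so in fresh stroke a pre-post change could be credited to OAKT; OAKT claims should rest on the randomised comparison

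*Protocol article*

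**What the plan says.** The article gives two accounts of the patient part of the study.

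- Study setting (and the Abstract, in the same terms) announces "a randomized controlled design within the 3 PSD groups (OAKT group, ocular acupuncture group, and kinesitherapy group"), and Interventions confirms that "PSD participants will be randomized to the ocular acupuncture (OA) group, the kinesitherapy (KT) group, or the OAKT group after enrollment". OA patients receive the acupuncture component "without any exercise training of any kind"; KT patients receive the exercise component "without ocular acupuncture stimulation".
- The Discussion, setting out how OAKT's effects on brain function, motor nerve function and motor dysfunction will be examined, describes "a case-control study in the PSD and HC groups as well as a self-control study in the PSD group". It does not mention randomisation there.

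The analysis sections differ in the same way. Clinical and electrophysiological data are compared between groups by t-test or ANOVA, with no covariates named. Neuroimaging data analysis names only paired t-tests on ReHo, and Functional neuroimaging outcomes says regions and clusters are recorded before and after the intervention.

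Under PSD participants, patients must "have unilateral dyskinesia and a fresh stroke diagnosis"; no onset window in days or weeks is given. The only untreated group is the healthy controls: "Healthy subjects will only get clinical, functional imaging, and electrophysiological evaluation without any therapy". Disease course appears once in the statistical methods: "Gender, age, and course will be included as covariates in a Pearson correlation study".

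**The concern.** The two accounts give different grounds for crediting an effect to OAKT. In a self-controlled design each patient's baseline is the comparator, which works only if the patient would otherwise stay stable. Patients soon after a stroke can be expected to change over 4 weeks on motor scales, MEP and brain activity whatever they receive. A within-arm change is therefore the sum of treatment and natural recovery, and nothing inside the arm separates the two.

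This matters most for imaging. The article presents itself as a mechanism study and ReHo is a central outcome, yet the one test named for it follows the self-control logic. If only that test is run, a ReHo change in the OAKT arm could be reported as OAKT's mechanism when it may be ordinary recovery that the OA and KT arms show as well.

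**Working it through.** **The plan's own figure.** Sample size gives 15 OAKT + 15 OA + 15 KT + 45 healthy controls: 3 × 15 + 45 = 90, which reproduces. The article gives no effect size, SD or recovery rate, so the recovery sizes below are assumptions, shown as a range.

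**Step 1: a within-arm test when treatment does nothing.** Inputs: n = 15 per arm (Sample size) and two-sided 0.05 (the threshold for clinical and electrophysiological data, used here for illustration). Let d be the assumed natural 4-week change divided by the SD of the change score. The paired t statistic is noncentral t with 14 degrees of freedom and noncentrality d√n, where √15 = 3.873. The critical value is 2.145. The voxel column uses one-sided 0.001 at a single voxel, before cluster correction.

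| Assumed d | Noncentrality d√15 | P(significant), single measure | P(voxel passes 0.001) |
|---|---|---|---|
| 0.3 | 1.162 | 0.19 | 0.02 |
| 0.5 | 1.936 | 0.44 | 0.07 |
| 0.8 | 3.098 | 0.82 | 0.31 |
| 1.0 | 3.873 | 0.95 | 0.55 |

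Only complete cases are analysed, so n may be smaller. With 12 per arm the single-measure probabilities are 0.16, 0.35, 0.71 and 0.88. The message does not change.

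**Step 2: the randomised contrast under the same recovery.** Change scores were simulated for two arms of 15, with a common recovery of 0.8 SD, no treatment difference and 20,000 trials per setting. The between-arm t-test rejected in 0.047 of trials when time since stroke was unrelated to the change, and in 0.051 when the correlation was 0.5. The within-arm test on the same data rejected in 0.825 and 0.823, in line with the 0.82 above. Shared recovery drives the paired test and leaves the between-arm test at its nominal 5%.

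**Step 3: time since stroke.** For two randomised arms of 15, the difference in mean time since stroke has standard error √(2/15) = 0.365 SD. The probability of a difference above 0.5 SD is 2 × [1 − Φ(0.5/0.365)] = 0.17 for a given pair of arms, and about 0.36 for at least one of the three pairs (simulated). Such imbalance is common. It is also random in direction and already counted in the standard error of the between-arm comparison, as Step 2 shows.

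**The case against.** The strongest reply is that the study is randomised. The Methods say so more than once, three arms are sized, and the term self-control occurs in one Discussion clause. Patients in every arm are measured before and after, so a within-patient element can coexist with randomisation. OA and KT are concurrent stroke patients who share natural recovery, and the clinical and MEP data are compared between groups. All of this stands, and Step 2 supports it.

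It does not cover ReHo, for which the article names no comparison of the randomised arms. Even if the paired test were read as matching patients to healthy controls, it would still not compare OAKT with OA or KT. A fuller plan may hold such a test, but the article is not silent here: it names the test, and it names one that cannot isolate OAKT.

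A reader might also infer three stronger things that the documents do not support:

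- *That natural recovery biases the OAKT-OA and OAKT-KT comparisons, or that an untreated stroke arm is needed.* It does not, and none is needed to estimate what OAKT adds to its components.
- *That time since stroke is left unbalanced.* Randomisation balances it in expectation. Chance imbalance is random error, and stratification may be described in the full protocol.
- *That the healthy controls' 4-week wait is meant to measure recovery.* No section says so; they are the case-control reference for abnormal function.

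**Conclusion.** The concern holds in a limited form. The article contradicts itself on the basis for OAKT claims, and the imaging analysis it names follows the weaker account. With no treatment effect, a single-measure paired test in 15 patients would be significant 19% to 95% of the time for an assumed natural change of 0.3 to 1.0 SD. The single-voxel figures are 2% to 55% before cluster correction. These sizes rest on assumed recovery, since the documents give no figure; the direction follows from recruiting patients with fresh stroke.

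The clinical and MEP comparisons between arms are sound in expectation. For them, the missing onset window and the absence of disease course from the comparison affect precision and the chance of imbalance with 15 per arm, and do not create bias. The point deserves correction because a pre-post ReHo change could otherwise be published as OAKT's mechanism, and because the remedy costs little.

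**What to change.** 1. **Discussion:** replace the description of the patient part as self-controlled with the randomised three-arm comparison of OAKT, OA and KT.
2. **Basis for claims:** state that OAKT effects on clinical, MEP and ReHo outcomes rest on the between-arm comparison of 4-week change. Report within-arm change descriptively, as treatment plus natural recovery.
3. **Neuroimaging data analysis:** add a between-arm ReHo test for OAKT-OA and OAKT-KT, either a group-by-time interaction or an ANCOVA on follow-up ReHo with baseline as covariate.
4. **Clinical and electrophysiological data analysis:** add baseline value and disease course as covariates in the OAKT-OA and OAKT-KT comparisons. The article does not define course. I take it to mean time since stroke, and the text should say so.

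Stratifying the randomisation by time since onset is optional.

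The cost is wording, one added imaging contrast and about one degree of freedom per covariate, using data already planned for collection. The between-arm test is also the harder one to pass: at 15 per arm its unadjusted power (two-sample t, 28 degrees of freedom) is 0.26, 0.56 and 0.75 for true differences of 0.5, 0.8 and 1.0 SD. That limit comes from the sample size. The paired test does not overcome it, because it answers a different question.

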## Confidentiality

The Hospital of Chengdu University of Traditional Chinese Medicine will maintain complete custody of all participant medical documents (study records/CRF, laboratory sheets, data CDs, etc.). Researchers, ethical committees, and statisticians will have access to medical records. Personal identity will not be disclosed in any public report on the results of this study. We will do everything within the law to protect the privacy of participants' personal medical information.

## Ancillary and post-trial care

The study team will bear all testing and treatment costs for this study.

Any potential harm from this study will be prevented and treated as best we can. The DMC will decide whether a study-related adverse event is caused by the trial's protocol or by the treatment if it occurs. In accordance with the Chinese Quality Management Standards for Drug Clinical Trials, the sponsor will pay for medical expenses and other financial compensation for any harm caused by the testing procedure.

## Ethics statement

The studies involving human participants were reviewed and approved by the Institutional Review Board of Chengdu University of Traditional Chinese Medicine has granted ethics approval for this study, which will be carried out in Aug 2022 in accordance with the Declaration of Helsinki's principles (reference number: 2022KL-027). The patients/participants provided their written informed consent to participate in this study.

